## Abstract

**Background:**

Compared to traditional thoracotomy, transapical transcatheter aortic valve implantation (TAVI) surgery offers reduced trauma and faster recovery, fostering the adoption of enhanced recovery after surgery (ERAS) protocols in cardiac surgery. Despite these advancements, postoperative pain management has received insufficient attention. The potential effects of multi-mode analgesia, including ultrasound-guided serratus anterior plane block (SAPB), on postoperative pain and early quality of recovery have not been widely studied, lacking comprehensive prospective evidence. Therefore, this study aims to investigate the impact of SAPB combined with general anesthesia on early recovery quality and analgesic efficacy in transapical TAVI patients.

**Methods:**

This prospective, randomized controlled study will enroll 70 patients undergoing transapical TAVI, randomly allocated to either the SAPB group or the control group. The primary outcome, assessed using Quality of Recovery-40 (QOR-40) scale, focuses on the quality of recovery at 24 h and 48 h postoperatively. Secondary outcomes include the visual analog scale (VAS) pain scores at rest and during coughing at 6 h, 12 h, 24 h, and 48 h after surgery, frequency of patient-controlled analgesia (PCA) utilization at 24 h and 48 h, opioid consumption at 24 h and 48 h, time and frequency of rescue analgesia and severe pain at 24 h and 48 h, incidence of nausea and vomiting at 48 h after surgery, and dosage of antiemetic drugs.

**Discussion:**

The purpose of our study is to evaluate the effects of ultrasound-guided SAPB combined with general anesthesia on postoperative early quality of recovery and analgesia in transapical TAVI patients. The results obtained may provide valuable insight for the implementation of multi-mode analgesia and enhanced ERAS in this specific patient population.

**Trial registration:**

China Clinical Trial Register ChiCTR2300068584. Registered on 24 February 2023.

## Introduction

### Background and rationale {6a}

Aortic valve disease is a prevalent valvular disorder encountered in clinical settings. Traditionally, the mainstay treatment for improving patient outcomes has been open-heart aortic valve replacement surgery, a procedure characterized by its highly invasiveness, requiring cardiopulmonary bypass and cardiac arrest. This approach, particularly challenging for elderly patients or those with multiple comorbidities, was associated with considerable early postoperative mortality rates. The breakthrough came with the first TAVI procedure in France in 2002, revolutionizing heart valve replacement through an interventional approach [1].

In recent years, TAVI has gained popularity, particularly suitable for high-risk patients [2]. Transapical TAVI presents several advantages, including operating in the direction of blood flow, shorter procedural distances, fewer intracardiac manipulations, reduced valve displacement risks, and the ability to overcome poor peripheral vascular conditions. Additionally, it significantly decreases contrast agent usage and exhibits lower incidences of stroke and organ embolisms [3]. Despite its advantages, including minimal incision and fast recovery compared to traditional surgery, postoperative pain remains a significant challenge.

Ultrasound-guided regional blocks, crucial components of multimodal analgesia, are widely utilized in routine clinical practice. SAPB is a chest wall nerve blockade technique [4], wherein local anesthetics (LAs) are diffused into the plane of serratus anterior muscle under ultrasound guidance. This effectively blocks the lateral cutaneous branches of intercostal nerves [5], infiltrating the long thoracic and thoracodorsal nerves, providing analgesia to the anterolateral chest wall. SAPB also assists in reducing the secretion of postoperative pain mediator, suppressing inflammatory responses, and decreasing inflammatory cytokine release. Additionally, it can reduce opioid consumption and its associated adverse effects, which is particularly relevant for elderly patients, especially those with severe systemic complications, thus contributing to the quality of postoperative recovery. Its application spans breast surgeries, thoracic surgeries, and rib fracture surgeries [6, 7]. However, the literature on the application of ultrasound-guided SAPB in minimally invasive cardiac surgeries, especially transapical TAVI, remains limited. Berthoud et al. [8] and Peng et al. [9] reported patients successfully completed apical TAVI surgery under SAPB due to serious complications. Furthermore, Berthoud et al. compared the therapeutic effects of SAPB and local incision infiltration for postoperative pain management in minimally invasive cardiac surgery. The results showed that SAPB can effectively alleviate postoperative pain in patients undergoing minimally invasive cardiac surgery and positively impact patient prognosis [10].

Furthermore, the integration of multimodal analgesia with regional block technique can improve analgesic efficacy while mitigating the adverse effects associated with opioid analgesics. However, achieving meaningful clinical outcomes require optimal postoperative recovery. Anesthesia and postoperative recovery constitute a multidimensional and intricate process. The QOR-40 scale is widely utilized in clinical settings to evaluate early postoperative recovery quality following anesthesia and surgery. Recognized for its suitability, feasibility, effectiveness, reliability, and precision, the QOR-40 scale is considered an optimal standard for assessing postoperative recovery [11]. Additionally, researchers have identified that preoperative low QoR-40 scores can predict poor postoperative recovery, and early effective interventions can enhance postoperative recovery quality, thus improving patient quality of life [12]. Therefore, establishing a direct correlation between ultrasound-guided SAPB and post-transapical TAVI surgery recovery quality necessitates further prospective data.

Our study seeks to examine the impact of ultrasound-guided SAPB on early postoperative recovery quality and analgesic efficacy in patients undergoing transapical TAVI procedures. By refining further multi-mode analgesia and ERAS protocols of this surgery, we aim to improve the postoperative rehabilitation quality and optimize the utilization of medical resources.

### Objectives {7}

The aim of this study is to investigate the influence of SAPB combined with general anesthesia on early recovery quality and analgesic efficacy in patients undergoing transapical TAVI.

### Trial design {8}

This is single-center, double-blind, randomized controlled trial aimed at investigating the impact of ultrasound-guided SAPB on early postoperative recovery quality and analgesic effectiveness in patients undergoing transapical TAVI. The study flow chart is depicted in Fig. 1. Our research received funding support from the National Natural Science Foundation of China (Project No. 82171265).

**Fig. 1 Fig1:**
[figure not shown]
Study flow chart

## Methods: participants, interventions, and outcomes

### Study setting {9}

The study will be conducted at the Second Affiliated Hospital of Army Medical University, Chinese People’s Liberation Army (PLA) (tertiary hospital), Chongqing, China. Participant enrollment began in February 2023. The protocol adheres to the principles outlined in the Declaration of Helsinki and follows the Standard Protocol Items: Recommendations for Interventional Trials (SPIRIT).

### Eligibility criteria {10}

#### Inclusion criteria

Patients will undergo a face-to-face screening 1 day prior to surgery based on the following eligibility criteria:Adult patients aged40–70 yearsASA II ~ IV classificationPatients planning to undergo transapical TAVI under general anesthesiaPatients expressing willingness to participate in this study and signed informed consent

#### Exclusion criteria

Patients meeting any of the following criteria will be excluded from the study:Allergy to LAsHistory of mental illness or taking psychotropic drugsSevere abnormalities in coagulation functionLong-term use of analgesics or sedativesHistory of drug abuse, alcohol, or opioid abuseRecent acute pain or chronic painPostoperative mechanical ventilation ≥ 24 hDecline to participate in the studyParticipants retain the right to withdraw from the study at their discretion for any reason or if researchers determine their inclusion is inappropriate

### Who will take informed consent? {26a}

Enrollment of eligible participants will be supervised by a designated member of the research team. Following a comprehensive oral explanation of the study, including its potential benefits and risks, patients or their legally authorized representative will be asked to sign the informed consent form approved by the institutional review committee. Participants and their legal authorized representatives will be informed that participation is entirely voluntary, and they have the right to withdraw from the trial at any time.

### Additional consent provisions for collection and use of participant data and biological specimens {26b}

Not applicable. We will not utilize the data and biological specimens of participants for ancillary studies.

### Interventions

#### Explanation for the choice of comparators {6b}

Currently, there is limited research on the analgesic effectiveness of SAPB in transapical TAVI. Establishing a direct correlation between SAPB and the quality of recovery following transapical TAVI surgery requires more prospective data for validation. This study aims to investigate the impact of SAPB on the postoperative early recovery quality and analgesic efficacy in patients undergoing transapical TAVI surgery, and to solve the contradiction between the patients who cannot tolerate large doses of opioids and the huge hemodynamic changes due to pain and subsequently affecting postoperative recovery quality. The study seeks to optimize the multi-mode analgesia and ERAS for this operation, with the goal of enhancing the postoperative recovery quality and optimizing the medical resources utilization.

Currently, other studies on regional block have used 0.9% saline as control, making it ethically feasible to have a blank control group in this study.

#### Intervention description {11a}

Ultrasound-guided SAPB will be conducted after induction of general anesthesia. Patient will be positioned supine with the upper limb abducted, and the ultrasonic probe will be located in the 5th intercostal space along the left axillary line. The probe’s direction will be adjusted to identify the tissue structures such as latissimus dorsi, pectoralis major, pectoralis minor, and serratus anterior. Using an in-plane technique, a 22-G nerve block needle will be advanced to the surface of the serratus anterior muscle and aspirated to ensure no blood and gas. Subsequently, 2 mL of local anesthetic mixture (0.4% ropivacaine + 10 mg dexamethasone) will be slowly injected. The injection will be performed while observing the spread of the anesthetic between the fascia layers, as indicated by a hypoechoic area on ultrasound, and additional mixture will be slowly injected. The control group will be given 40 mL normal saline.

#### Criteria for discontinuing or modifying allocated interventions {11b}

Withdrawal criteria are as the follows:Patient or legal representative requests to withdraw from the study.Changes in the surgical procedure may occur during surgery.The investigator may decide to terminate the trial due to other unforeseen reasons.

#### Strategies to improve adherence to interventions {11c}

All SAPB procedures, surgeries, and assessments will be consistently performed by the same anesthesiologist, surgeon, and assessor, respectively. Randomization and monitoring processes will be conducted by independent researchers to ensure fairness and protocol adherence. The principal investigator will be responsible for all aspects of the recruitment process and any amendment to the study. All the experiments will strictly adhere to the research plan, ensuring reliability and effectiveness of our results.

#### Relevant concomitant care permitted or prohibited during the trial {11d}

Patients will be prepared in accordance with cardiopulmonary bypass, and standard monitoring will be established, including electrocardiograph (ECG), non-invasive blood pressure (NIBP), pulse oxygen saturation (SpO_2_), body temperature (T), bispectral index (BIS), and cerebral oxygen, with an external automatic defibrillation patch attached. Radial artery and right internal jugular vein catheterization, under local anesthesia, will facilitate monitoring of invasive arteriovenous pressure. General anesthesia induction will involve midazolam (0.03 ~ 0.08 mg/kg), etomidate (0.2 ~ 0.6 mg/kg), rocuronium (0.6 ~ 0.9 mg/kg), and sufentanil (0.3 ~ 0.4 μg/kg). Tracheal tubes will be inserted when the BIS value decreased to 40 ~ 50, initiating mechanical ventilation with a tidal volume of 6 to 8 mL/kg, respiratory rate of 12 to 15/min, and a 1:1 air-oxygen mixture, maintaining ETCO_2_ between 35 and 45 mmHg.

The anesthesia will be maintained with propofol (4 ~ 6 mg/kg/h), remifentanil (0.08 ~ 0.3 µg/kg/min), and sevoflurane (1 ~ 2 vol%). Heart rate and mean arterial pressure will be maintained within ± 20% of baseline, except during rapid ventricular pacing. Blood potassium level will be maintained between 4.5 and 5.5 mmol/L and BIS will be kept between 40 and 60 throughout operation.

Patients will be delivered to cardiac surgery intensive care unit postoperatively for standardized monitoring and management. A postoperative patient-controlled intravenous analgesia (PCIA) regimen will be established as part of a multimodal pain regimen, with sufentanil (2.5 µg/mL, limit dose 200 µg) combined with dexmedetomidine (3 µg/mL, limit dose 200 µg) and tropisetron 5 mg. The PCIA pump will be programmed for a 2 mL bolus with a lockout interval of 15 min and a basal infusion of 4 mL/h. Rescue analgesia will include paracetamol and tramadol hydrochloride tablets (one tablet, p.o) for VAS > 4 at rest, and 1 mg of hydromorphone intravenously for severe pain (VAS > 7). Patients will be educated on PCIA pump usage.

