### Outcomes {12}

#### Primary and secondary outcomes

The primary outcome will assess the quality of recovery at 24 h and 48 h, measured using the QoR-40 scale [11, 13].

The secondary outcomes include:VAS pain scores: assessment at rest and during coughing at 6 h, 12 h, 24 h, and 48 h post-surgery [9]Frequency of PCA utilization: evaluation at 24 h and 48 h following surgery [14, 15]Opioid consumption: quantification at 24 h and 48 h post-surgery [14, 15]Time and frequency of rescue analgesia and severe pain: analysis at 24 h and 48 h after surgery [16]Incidence of nausea and vomiting: determination at 48 h post-surgery, along with the dosage of antiemetic drugs [15]

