### Sample size {14}

The sample size calculation is based on the primary outcome. According to a prior publication, where mean of group 1 was 167 and the mean of group 2 was 184, with known group standard deviations of 23 [13], a sample size of 33 for each group (66 in total) will be required to achieve a power of 80% to detect the difference at a two-side *α* level of 0.05, taking into account a dropout rate of 10%. Ultimately, we plan to include 35 participants in each group.

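### The pump's basal rate alone passes the printed 200 µg limits before 24 h, so the pump figures do not fit together or with the 24 h and 48 h opioid and PCA outcomes

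*Protocol article*

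**What the plan says.** Section {11d} of the protocol article describes one postoperative pump regimen, with no difference by arm. The mixture contains "sufentanil (2.5 µg/mL, limit dose 200 µg") and "dexmedetomidine (3 µg/mL, limit dose 200 µg"). The settings are: "The PCIA pump will be programmed for a 2 mL bolus with a lockout interval of 15 min and a basal infusion of 4 mL/h".

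The section does not say what period the limits cover, what happens when one is reached, whether the pump is refilled, or how soon after surgery it starts.

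Opioid is also available outside the pump: "Rescue analgesia will include paracetamol and tramadol hydrochloride tablets (one tablet, p.o) for VAS > 4 at rest", and intravenous hydromorphone 1 mg for severe pain.

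The secondary outcomes in section {12} include "Opioid consumption: quantification at 24 h and 48 h post-surgery" and "Frequency of PCA utilization: evaluation at 24 h and 48 h following surgery". Table 1 schedules both at the same two times.

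**The concern.** The concentrations, limits and basal rate are printed side by side, and together they imply that the limits are reached before the first of the two outcome times, even in a patient who never presses the button.

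If the limits are enforced, the total pump dose is set by the limit and not by the patient's pain. A block that reduces demand would then leave no trace in the pump part of opioid consumption, and bolus counts would stop accruing when the pump stops. If the limits are not enforced, or the pump is refilled, the printed limit does not describe what patients receive.

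The Discussion names opioid consumption and pump presses among the measures of the block's analgesic effect, so it matters what these two outcomes can show.

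**Working it through.** The 200 µg limits are stated inputs, not derived figures, so there is no calculation in the article to reproduce. All inputs come from section {11d}: sufentanil 2.5 µg/mL, dexmedetomidine 3 µg/mL, limit 200 µg for each, basal 4 mL/h, bolus 2 mL, lockout 15 min.

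**Time to the limit, no bolus** = limit / (concentration × basal rate)
- Sufentanil: 4 × 2.5 = 10 µg/h; 200 / 10 = 20.0 h; volume 200 / 2.5 = 80 mL.
- Dexmedetomidine: 4 × 3 = 12 µg/h; 200 / 12 = 16.7 h; volume 200 / 3 = 66.7 mL.

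**Time to the limit, maximum demand.** Four boluses an hour give 4 × 2 = 8 mL/h; with basal flow, 12 mL/h.
- Sufentanil: 80 / 12 = 6.7 h.
- Dexmedetomidine: 66.7 / 12 = 5.6 h.

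**Basal dose if nothing stops the pump** = concentration × 4 mL/h × time
- Sufentanil: 240 µg at 24 h, 480 µg at 48 h.
- Dexmedetomidine: 288 µg at 24 h, 576 µg at 48 h.

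**Which limit acts first.** The 80 mL that holds 200 µg sufentanil holds 80 × 3 = 240 µg dexmedetomidine. If the dexmedetomidine limit stops the pump at 66.7 mL, the sufentanil delivered is 66.7 × 2.5 = 166.7 µg.

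**Pump sufentanil under each reading of the limit**, with a prompt start and no interruption:

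| Reading | At 24 h | At 48 h |
|---|---|---|
| Total stop | 200 µg (166.7 µg if the dexmedetomidine limit acts first) | the same |
| Stop per 24 h from pump start | 200 µg (166.7 µg) | 400 µg (333 µg) |
| Pump refilled, no stop | at least 240 µg, depends on demand | at least 480 µg, depends on demand |

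In the first two rows the value is the same for every patient in both arms. In the third it can vary, but it is above the printed 200 µg.

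**What a prompt start means.** To reach the limit by 24 h with no bolus, the pump must start within 24 − 20 = 4 h of surgery (sufentanil limit) or 24 − 16.7 = 7.3 h (dexmedetomidine limit). Boluses bring the time forward and so relax this condition. The same 4 h and 7.3 h apply at 48 h under a daily limit. Under a total limit the 48 h value needs a start only within 48 − 20 = 28 h, or 48 − 16.7 = 31.3 h.

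**Bolus counts under an 80 mL stop.** If the pump runs out T hours after it starts, delivered boluses = (80 − 4T) / 2. This is 0 at T = 20 h and about 27 at T = 6.7 h. Because T itself depends on demand, the count still varies between patients, but it is truncated at run-out.

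**The case against.** The strongest reply is that the article never says the limit is a hard stop over 24 h or longer. It could be the content of one filling, with refills; consumption is then not capped. It could also be a short-window limit. Maximum delivery is 12 × 2.5 = 30 µg/h sufentanil, or 120 µg in 4 h, so a limit over such a window would never bind. The full protocol may settle this. The reply stands in part: a cap cannot be asserted as fact. It does not remove the problem, because the article states neither a refill nor a short window, and on its plain wording the basal rate passes the printed limit before the first outcome time.

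Start time is a second fair point. The exclusion criteria remove only patients ventilated for 24 h or more, so some retained patients may start the pump late or have it interrupted, and would be below the limit at 24 h.

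A reader might infer more than the documents support:
- **That opioid consumption must be equal in the two arms.** The outcome is not defined as pump sufentanil only, and rescue tramadol and hydromorphone lie outside the pump limit.
- **That PCA counts carry no information.** They are truncated, not empty, as the bolus formula shows.
- **That the pump regimen and the outcomes cannot both be carried out.** They can; at worst the pump component fails to discriminate.
- **That the two limits contradict each other.** Two drugs may have separate ceilings, and the one reached first acts. What is missing is a statement of what then happens to the mixture.
- **That the primary outcome is undermined.** QoR-40 is not computed from pump totals, the regimen is common to both arms, and actual run-out is not established by the text.

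**Conclusion.** The point holds as an unreconciled set of printed figures. Basal flow alone reaches the limits at 20.0 h and 16.7 h, and 48 h of basal flow is 480 µg sufentanil and 576 µg dexmedetomidine against limits of 200 µg each.

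The statistical consequence is conditional. It requires that the limit is a total or per-24-h stop, that there is no refill, and that the pump starts within about 4 h of surgery (sufentanil limit) or 7.3 h (dexmedetomidine limit) and runs without interruption. Then the expected between-arm difference in pump sufentanil at 24 h is zero whatever the block does. The same follows at 48 h, at the same level under a total limit or at twice that level under a daily one.

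This should be fixed, but it is confined to two secondary outcomes, and within opioid consumption to the part delivered by the pump.

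**What to change.** The clinical team should reconcile the concentrations, the meaning and period of the limit, the consequence of reaching it, any refill rule and the basal rate in section {11d} with the 24 h and 48 h outcomes in section {12}. Which of these should change is a clinical decision, and no value is proposed here.

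For the data and analysis:
- Take pump start, stop and refill times from the pump record for every patient. The Recruitment section reports 50 participants already enrolled of 70 planned, so this must include those already treated.
- Count rescue tramadol and hydromorphone in the opioid consumption outcome, on one conversion scale fixed before unblinding.
- Report basal and patient-triggered sufentanil separately, so that a fixed basal dose does not hide a difference in demand.
- Give PCA demand per hour of pump operation as well as the raw count.

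If the analysis plan already contains these rules, only the reconciliation and the pump times remain. The cost is a protocol clarification, some extra data extraction and a few more analyses. No extra patients are needed.

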#### Provisions for post-trial care {30}

All study participants will receive standard care. We will closely monitor them throughout the postoperative period to promptly identify any potential complications and implement intervention measures as necessary.

### Outcomes {12}

#### Primary and secondary outcomes

The primary outcome will assess the quality of recovery at 24 h and 48 h, measured using the QoR-40 scale [11, 13].

The secondary outcomes include:VAS pain scores: assessment at rest and during coughing at 6 h, 12 h, 24 h, and 48 h post-surgery [9]Frequency of PCA utilization: evaluation at 24 h and 48 h following surgery [14, 15]Opioid consumption: quantification at 24 h and 48 h post-surgery [14, 15]Time and frequency of rescue analgesia and severe pain: analysis at 24 h and 48 h after surgery [16]Incidence of nausea and vomiting: determination at 48 h post-surgery, along with the dosage of antiemetic drugs [15]

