### Statistical methods

#### Statistical methods for primary and secondary outcomes {20a}

All normally distributed continuous variables will be expressed as mean ± standard deviation and analyzed with Student’s *t*-test. For non-normal distributed data, the Mann–Whitney *U* test will be used, and results will be presented as median and interquartile interval. Categorical variables will be described with frequencies (%) and compared using the chi-square test or Fisher’s exact test. A 95% confidence interval (CI) for differences in means (for continuous outcomes) or relative risks (for categorical outcomes) will be calculated. A *P* value < 0.05 will be considered statistically significant. Statistical analyses will be performed using SPSS software version 26 (IBM, New York, USA).

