Dexamethasone, a long-acting synthetic glucocorticoid, is utilized as an adjuvant to LAs to extend their duration [20, 21] and mitigate postoperative nausea, vomiting, and chills. In our study, we aim to enhance the duration of analgesia and achieve a more pronounced and sustained effect by combining dexamethasone with ropivacaine. However, it is necessary to monitor the potential side effects of dexamethasone, such as hyperglycemia, especially in this vulnerable patient population. Therefore, a detailed monitoring plan should be established to effectively track and manage these potential adverse effects through blood gas analysis or blood glucose measurement.

Postoperative recovery quality, a complex and dynamic process, is a critical patient-centered outcome, which can be evaluated from the aspects of physiology, psychology, and social adaptation. QOR-40 scale is the best tool to evaluate the quality of early postoperative recovery after clinical intervention based on clinical and research verification. It includes five dimensions: physical comfort, pain, emotional state, physical independence, and psychological support. With good validity, reliability, responsiveness, and clinical acceptability, QOR-40 is widely used in various perioperative environments [13, 22]. Through this comprehensive assessment, our study aims to provide valuable prospective evidence on regional analgesia efficacy in this population. During the recruitment process, we found that ensuring consistent and accurate patient responses can be challenging, especially considering the elderly population involved. To assist patients in completing the QOR-40, our researchers need to use more simplified language to help elderly patients understand, thereby improving data quality.

We acknowledge some limitations in our study. Firstly, our primary outcome is assessed at 24 and 48 h postoperatively, providing insights into early recovery but lacking long-term follow-up to evaluate sustained intervention impact and potential complications. In addition, while we explore the effectiveness of SAPB, uncertainty persists regarding the optimal concentration and dosage of LAs and adjuvants in the block. Future high-quality research is warranted to explore this aspect further, elucidating the most effective drug combinations and furnishing instructive insights for clinical practice.

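### QoR-40 at 24 h and at 48 h are both primary with no rule for deciding success, while the stated 5% error and 80% power fit one comparison only

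*Protocol article*

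**What the plan says.** - **Primary outcome.** Under Primary and secondary outcomes: "The primary outcome will assess the quality of recovery at 24 h and 48 h, measured using the QoR-40 scale". The abstract agrees (it "focuses on the quality of recovery at 24 h and 48 h postoperatively"), and so does the Discussion ("our primary outcome is assessed at 24 and 48 h postoperatively"). None of the three ranks the hours, combines them, or says whether one or both must show a difference.
- **Tests.** Under Statistical methods {20a}: "All normally distributed continuous variables will be expressed as mean ± standard deviation and analyzed with" Student's t-test, with the Mann-Whitney U test for non-normal data. This section covers the primary and the secondary outcomes. It names no repeated-measures or joint test.
- **Threshold.** The same section: "A *P* value < 0.05 will be considered statistically significant". No order, split or adjustment follows.
- **Sample size {14}.** Group means of 167 and 184 with SD 23, taken from a prior publication, lead to "a sample size of 33 for each group (66 in total) will be required to achieve a power of 80% to detect the difference" at two-sided 0.05, allowing for 10% dropout. The number is then raised to 35 per group. The hour at which the 17-point difference was seen is not stated.

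**The concern.** There are two primary comparisons, one alpha of 0.05 and one power calculation, and these do not fit together. Suppose the 24 h comparison is significant and the 48 h comparison is not, or the reverse. Nothing in the article says whether the trial has then succeeded. The answer could be chosen after the results are known, and in that case the published P < 0.05 would not carry the 5% error rate on which the sample size was built. If both hours were meant to be required, the error rate is safe, but the 80% power was calculated for something easier.

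**Working it through.** **Inputs from Sample size {14}.** Difference 184 − 167 = 17; SD 23; two-sided alpha 0.05; power 80%; dropout 10%; 35 recruited per group. Standardised effect d = 17/23 = 0.739.

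**Assumed inputs, not in the documents.** A 24 h to 48 h correlation of 0.5 to 0.8 (wider values also shown), and the same 17-point effect and SD 23 at both hours.

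**1. Reproducing the plan's figure.** n per group = 2(1.960 + 0.842)² / 0.739² = 28.7, so 29. With dropout, 29/0.9 = 32.2, so 33. This matches the stated 33 per group exactly, so the 80% power belongs to one test at 0.05.

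**2. Power of that one test at the planned size.** Evaluable per arm = 35 × 0.9 = 31.5. The t-test power is 82% at 31.5 and 86% at 35.

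**3. If either hour suffices.** False-positive rate = 1 − P(|Z₁| < 1.96 and |Z₂| < 1.96), with (Z₁, Z₂) bivariate normal with correlation ρ. At ρ = 0 this is 1 − 0.95² = 9.75%, which is the ceiling.

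| ρ (assumed) | False-positive rate |
|---|---|
| 0 | 9.75% |
| 0.5 | 9.1% |
| 0.7 | 8.3% |
| 0.8 | 7.8% |
| 0.9 | 7.0% |

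The rate tends to 5% as ρ tends to 1. Under this rule the power to win at least once is P₁ + P₂ − P(both). At 31.5 per arm and ρ = 0.5 that is 0.823 + 0.823 − 0.719 = 0.927. Over ρ = 0.5 to 0.8 it is about 89% to 93%, so power is not short here.

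**4. If both hours are required.** The type I error is at most 5%. Joint power is the bivariate normal probability that both tests reject, with each test's t-test power as its margin:

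| ρ (assumed) | 31.5 per arm | 35 per arm |
|---|---|---|
| 0.5 | 72% | 77% |
| 0.7 | 74% | 79% |
| 0.8 | 76% | 81% |

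**5. If alpha is split equally (Bonferroni, 0.025 each).** The t-test power per comparison is 74% at 31.5 per arm and 79% at 35.

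**The case against.** The strongest reply is that only a condensed article is at hand. An alpha split, a testing order or a joint model is often placed in the statistical analysis plan, and the sentence on continuous variables is generic and does not mention QoR-40. That is fair as far as it goes: a rule may exist elsewhere. But the article itself fixes the primary outcome, the tests, the threshold and the power claim. Which hour decides the trial is part of defining the primary outcome, and the power claim is worked out for one comparison without saying which.

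A reader might infer that the false-positive rate simply is 8% to 9%. The documents do not support that. It needs an either-hour rule, which is not stated, and a correlation, which is not given.

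A reader might also infer that the trial suffers inflated error and low power together. No single rule examined here produces both. The either-hour rule inflates alpha but leaves power above 80%. The both-required rule and the equal split control alpha but lose power.

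The power loss is also modest. The article expects very few missing primary values and would impute them. With all 35 per arm evaluable, the both-required rule (77% to 81%) and the equal split (79%) come close to 80%.

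**Conclusion.** The point stands in conditional form. As published, two unranked primary comparisons share one threshold of 0.05 and one power calculation, so neither the error rate nor the power of the primary analysis is defined.

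- **Either hour suffices:** the error rate exceeds 5% and cannot exceed 9.75%.
- **Both hours required:** the error rate holds, and joint power falls below 80% at the dropout-adjusted size.

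The reproduction of 33 per group and the 9.75% ceiling need no outside assumption. The narrower ranges rest on the assumed correlation, and the joint-power figures also rest on an equal effect and SD at both hours. The documents do not show whether the 17-point difference was a 24 h or a 48 h value, so neither hour can be inferred to be the intended one. Because the gap decides whether the trial is called positive, it should be closed before unblinding.

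**What to change.** By a documented amendment before unblinding:

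1. Name QoR-40 at one hour (for example 24 h) as the single primary outcome, tested at two-sided 0.05.
2. Test the other hour only if the first is significant (fixed sequence). This keeps the overall error rate at 5%.
3. In Sample size {14}, state which hour the 167 vs 184 difference comes from, and that the 80% power refers to the primary-hour comparison only. If the source hour differs from the chosen primary hour, say why the difference is expected to carry over.

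A both-required rule or an alpha split would also be valid, at the power shown above.

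**Cost.** No extra patients. If the 17-point assumption holds at the chosen hour, power stays at about 82% with 31.5 evaluable per arm. The downside is that no confirmatory claim can be made at the second hour if the first fails. The change needs ethics review and a revised plan under the article's amendment procedure. With 50 of 70 participants already recruited at the time of writing, the record should show that it was made without sight of results by group. No interim analysis is planned, and patients and outcome assessors stay blinded until the analysis is complete, so this should still be possible.
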